### Sample size estimates

Statistical power and appropriate effect size estimates are based on published recommendations [45] and unpublished pilot data using this protocol collected by our group. A sample size of 128 participants (64 in each treatment arm) provides ≥ 80% power (with a Bonferroni-adjusted significance level of 0.013 allowing for multiple comparisons) to detect improvements of approximately 1 standard deviation in sleep quality (2-point reduction), fatigue (3-point reduction), and functioning (8-point improvement) measures in the intervention arm [46]. This conservative estimate will allow for an attrition rate of up to 10%.

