### Outcomes

The primary outcomes for this study are changes in self-reported sleep quality, symptoms, and functioning. These will be assessed by self-report measures at the 4-week assessment. Secondary outcomes are changes in HRV and interventional acceptability.

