### Data analysis plan

The outcome variable (change scores) will be analysed using linear mixed modelling. Treatment arm (intervention/control) and clinical condition (MDD/CFS) will be included in models as a dichotomous between-subjects variable. Baseline values of the outcome variable will also be included as a covariate (to control for chance differences between treatment arms at baseline). Bivariate associations between demographic measures and outcome variables will be explored using Pearson pairwise correlations. The outcome of these analyses will inform about additional variables to be included in multivariate models as covariates.

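### The only multiplicity rule stated is single-step Bonferroni at 0.013; Holm's step-down test gives the same error control, never has less power, and would help if effects are moderate

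*Protocol article*

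**What the plan says.** Under Sample size estimates, the article plans 128 participants, 64 per arm. The effects it is sized for are given as "improvements of approximately 1 standard deviation in sleep quality (2-point reduction), fatigue (3-point reduction), and functioning (8-point improvement) measures". Power is put at 80% or more, "with a Bonferroni-adjusted significance level of 0.013 allowing for multiple comparisons". It allows for up to 10% attrition. Neither the number of comparisons nor the overall alpha is given.

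Under Outcomes: "The primary outcomes for this study are changes in self-reported sleep quality, symptoms, and functioning". That is three domains, assessed at 4 weeks.

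Under Data analysis plan: "The outcome variable (change scores) will be analysed using linear mixed modelling", with treatment arm, clinical condition and the baseline value in the model. This section gives no significance threshold and no multiplicity procedure. The 0.013 in the sample size section is therefore the article's only statement on multiplicity, and no stepwise test is mentioned.

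**The concern.** Single-step Bonferroni holds every comparison to the strictest threshold, whatever happens on the others. Holm starts at the same threshold, 0.05/m. After each rejection it relaxes to 0.05/(m-1), then 0.05/(m-2), and so on down to 0.05. It protects the family-wise error equally well under any dependence and cannot reject fewer hypotheses.

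The trial's hypothesis is that sleep quality, fatigue, symptoms and functioning all improve. Several true effects at once is the setting in which a step-down test recovers power. At stake is the chance of confirming the second, third or later outcome if effects turn out smaller than planned. No false-positive risk is at stake.

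**Working it through.** **Inputs from the article.** n = 64 per arm (about 58 after 10% attrition); alpha = 0.013 per comparison; effect about 1 SD; power at least 80%.

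**Assumptions not in the article.** Two-sided tests; SD equal to the stated improvement; no precision gain from baseline adjustment; m = 3 or 4 primary tests; equal correlation between test statistics; the same true effect on all outcomes unless stated.

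**1. The plan's own power.** Per outcome, power ≈ Φ(d·√(n/2) − z), with z = 2.484 for two-sided 0.013.
- 64 per arm, d = 1: √32 = 5.657; Φ(5.657 − 2.484) = Φ(3.173) = 99.9%.
- 58 per arm, d = 1: √29 = 5.385; Φ(2.901) = 99.8%.

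The floor of 80% is met with a wide margin. Power of exactly 80% at 1 SD needs n = 2(2.484 + 0.842)² = 22.1, so 23 per arm. Conversely, with 64 per arm, 80% power corresponds to d = (2.484 + 0.842)·√(2/64) = 0.59 SD.

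**2. Holm against Bonferroni at the planned effect.** In simulation (200,000 runs per setting, equicorrelated normal statistics), Holm gives 99.97 to 99.99% at 1 SD with 64 per arm. The gain over 0.013 is 0.05 to 0.07 point. With 58 per arm it is 0.11 to 0.18 point.

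**3. The same comparison at moderate effects.** Power per outcome with 64 per arm, Bonferroni at 0.05/m against Holm at family-wise 0.05:

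| True effect | m | Correlation | Bonferroni 0.05/m | Holm | Gain (points) |
|---|---|---|---|---|---|
| 0.50 SD | 3 | 0.3 | 66.7% | 75.0% | 8.3 |
| 0.50 SD | 3 | 0.5 | 66.9% | 74.6% | 7.7 |
| 0.50 SD | 3 | 0.8 | 66.8% | 73.2% | 6.5 |
| 0.50 SD | 4 | 0.3 | 62.9% | 72.6% | 9.7 |
| 0.50 SD | 4 | 0.5 | 63.0% | 71.9% | 8.9 |
| 0.50 SD | 4 | 0.8 | 62.9% | 70.6% | 7.7 |
| 0.588 SD | 3 | 0.3 | 82.4% | 89.1% | 6.7 |
| 0.588 SD | 3 | 0.5 | 82.3% | 88.4% | 6.1 |
| 0.588 SD | 3 | 0.8 | 82.4% | 87.3% | 4.9 |
| 0.588 SD | 4 | 0.3 | 79.6% | 88.0% | 8.4 |
| 0.588 SD | 4 | 0.5 | 79.6% | 87.2% | 7.5 |
| 0.588 SD | 4 | 0.8 | 79.8% | 85.7% | 5.9 |

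For four outcomes at 0.5 SD and correlation 0.5, the chance that all four are significant is about 32% with Bonferroni and 54% with Holm. Bonferroni would need about 76 per arm to match Holm's per-outcome power at 64. With 58 per arm, power per outcome is 57.8% against 66.8%.

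**4. Only one outcome with a true effect.** Near the 80% point, Holm adds 0.14 point for m = 3 (83.41% to 83.55%) and 0.08 point for m = 4 (80.60% to 80.69%).

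**5. The threshold.** 0.05/4 = 0.0125, which rounds up to 0.013, and 4 × 0.013 = 0.052. For the three named domains, 0.05/3 = 0.0167 and 3 × 0.013 = 0.039.

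**The case against.** The strongest reply is that nothing here is wrong. Bonferroni is valid and simple, and it yields simultaneous confidence intervals that match its decisions. At the effect the trial is planned for, the two procedures are indistinguishable. All of this stands. The 0.5 to 0.6 SD range is an assumption. What supports it is that the Background calls the effects of comparable interventions small to moderate, and that 80% power with 64 per arm corresponds to about 0.59 SD.

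A second reply is that the 0.013 sits in a power statement and the Data analysis plan sets no threshold, so an analysis plan that is not shown may already use a stepwise test. That also stands in part: sizing on the Bonferroni level is compatible with testing by Holm. A reader might infer that every primary comparison is bound to be judged at 0.013, but the article does not say so. It remains the only rule the public document gives.

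Three stronger readings are tempting and not supported:
- **A flat loss of about 9 points per outcome.** That size needs effects near 0.5 SD on all outcomes. At the plan's 1 SD the loss is under 0.1 point.
- **A family-wise error above 5% through rounding.** This needs exactly four tests. The article names three domains, for which the bound is 0.039, stricter than necessary.
- **A larger gain because the scores are correlated.** The opposite holds. With four outcomes at 0.5 SD, the gain falls from 10.8 points at correlation 0 to 7.7 at 0.8. Shared true effects help; correlation between scores slightly reduces the gain.

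**Conclusion.** The point holds as an avoidable inefficiency, not as an error. Single-step Bonferroni is the only multiplicity rule in the article, and Holm offers the same family-wise protection with power that is never lower.

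The size is conditional. It is negligible at the planned 1 SD, about 5 to 10 points per outcome for true effects of 0.5 to 0.6 SD on all of three or four outcomes with correlations of 0.3 to 0.7, and close to nil if a single outcome responds. These gains compare Holm at 0.05 with Bonferroni at 0.05/m. Setting Holm at 0.05 against 0.013 for three outcomes would overstate the gain, because that rule spends only 0.039. Effect, correlation and m are assumptions; the article gives neither a correlation nor the number of tests.

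**What to change.** Add one sentence to the Data analysis plan: the named primary outcomes are tested with Holm's procedure at family-wise 0.05, at 0.05/m, then 0.05/(m-1), and so on to 0.05, with m the stated number of primary tests and no threshold rounded up. For m = 3 the steps are 0.05/3, 0.025 and 0.05; for m = 4 they are 0.0125, 0.05/3, 0.025 and 0.05.

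Keep the sample size on the Bonferroni first step, which is conservative. Report Bonferroni-level confidence intervals beside the Holm decisions.

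No new participants or data are needed, and the sentence should be in place before the treatment coding is opened. The small downside is that some intervals may include no effect for an outcome that Holm declares significant, which the text should say.

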### Data collection

All consenting participants complete two face-to-face assessments, 4 weeks apart, and a further set of questionnaires completed online 8 weeks after the initial assessment (Fig 2). At the first assessment (lasting approximately 90 min), participants’ demographic, health, and symptom information are documented. Autonomic activity at rest and in response to each of the relaxation methods (see below) is recorded. Results from this initial testing determine which method participants randomised to the intervention group will practise daily during the 4-week intervention (i.e. the method which induced the greatest increase in HRV for that participant). Before leaving, all participants are fitted with a non-invasive ambulatory bioharness (Equivital EQ-02, Hidalgo Ltd., Cambridgeshire, UK) for 24-h monitoring and issued a sleep/activity/symptom log to complete over the next 4 weeks (see subsequent paragraphs). The second assessment lasts approximately 45 min and consists of a briefer version of the initial assessments (i.e. assessment of health, symptoms, and autonomic activity). Those in the control arm will be offered the personalised intervention at this assessment. The third assessment consists of online self-report measures, including questionnaires about the participant’s sleep, symptoms, and current frequency of relaxation practice. This will allow us to assess possible enduring benefits of the intervention in the active group, and to determine whether subjective improvements are evident in the monitoring group who will have practised their assigned intervention for 4 weeks. Participants will be emailed a personalised link to the online questionnaire. An automated reminder email will be sent after 1 week and again after 2 weeks, if the participant has not completed the questionnaire. The online nature of this assessment will reduce inconvenience for the participants and hence minimise attrition.

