### Randomisation, allocation, and blinding

A permuted block randomisation sequence (block sizes of four), stratified by clinical condition, was generated using Stata 13 by the study biostatistician (EC) prior to trial commencement. The randomisation sequence is stored in a password-protected file not accessible to the researcher responsible for enrolling and assessing participants. Treatment allocation remains concealed until immediately before a participant’s first assessment, at which time the assessing researcher is informed of the allocation by the study administrator. Due to the nature of the intervention, both the participant and assessing researcher are not blinded to group assignment. During primary data analysis, the biostatistician will be blinded to treatment group (i.e. by using unlabelled numerical coding for the treatment group variable within the dataset, recoverable by the study administrator).

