#### Autonomic assessment

Laboratory-based autonomic measures include three-lead electrocardiogram (ECG) and respiration (via a strain gauge transducer) recorded at 1 kHz using PowerLab and LabChart Pro 8 (ADInstruments, Bella Vista, Australia). To obtain a baseline assessment of cardiac autonomic functioning, participants are asked to relax in a semi-reclined position for 10 min, in silence. Autonomic responses are also measured during the presentation of each of the three relaxation methods (each ~ 10-min duration). Immediately after the assessment, data are processed and analysed using the LabChart HRV 2.0 module to determine the participant’s baseline HRV and his/her response during each of the relaxation methods to allow selection of the method that induced the largest increase in HRV response for that participant.

Continuous 24-h monitoring of autonomic activity (including during nocturnal sleep) is achieved via a lightweight bioharness system (Equivital, Hidalgo) at baseline and at 4 weeks. Participants are fitted with a non-invasive chest harness consisting of a two-channel ECG (sampling rate 256 Hz), respiratory belt (25.6 Hz), skin temperature sensor (25.6 Hz), and tri-axial accelerometer (25.6 Hz, enabling detection of body orientation and movement). The overnight data are extracted and processed using LabChart Pro.

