### Intervention

#### Personalised relaxation intervention

Participants allocated to the intervention are assigned to practise the method which generated the greatest relaxation response (as quantified by an increase in HRV) relative to their resting baseline, thus optimising de-arousal.

Participants have free online access to their assigned method and are able to download the recordings (10-min segments) to their smartphone or media device, or if preferred a portable media player is provided. A number of similar variants of their assigned method are offered to maximise enjoyment and prevent negative effects of frequent repetition. Participants are instructed to practise their assigned method at a minimum before bedtime every evening for 4 weeks, but may use the method at other times if desired.

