#### Sleep and symptom monitoring

Participants in the control condition complete the same assessments as the intervention group at baseline and at the 4 week follow-up. Control participants are informed that 4 weeks of symptom monitoring will precede allocation of a personalised relaxation method. During this period they are asked not to practise mindfulness or meditation activities. At the completion of the second assessment, participants in the control group will be offered their personalised intervention.

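### The baseline night of HRV is recorded after allocation and, as scheduled, on the intervention arm's first practice evening, so it is not a pre-treatment value for nocturnal HRV

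*Protocol article*

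**What the plan says.** The order of events has to be assembled from several sections of the protocol article.

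- Randomisation, allocation, and blinding: "Treatment allocation remains concealed until immediately before a participant’s first assessment". The assessing researcher therefore knows the arm before anything is recorded.
- Autonomic assessment, on selecting the method: "Immediately after the assessment, data are processed and analysed using the LabChart HRV 2.0 module". The purpose is to find the method with the largest HRV rise for that participant.
- Data collection, on the end of that visit: "Before leaving, all participants are fitted with a non-invasive ambulatory bioharness".
- Personalised relaxation intervention: "Participants are instructed to practise their assigned method at a minimum before bedtime every evening for 4 weeks".
- Data collection, on the interval: "All consenting participants complete two face-to-face assessments, 4 weeks apart".
- Autonomic assessment, on the 24-hour recordings: they are made "via a lightweight bioharness system (Equivital, Hidalgo) at baseline and at 4 weeks".
- Sleep and symptom monitoring: "At the completion of the second assessment, participants in the control group will be offered their personalised intervention".
- Outcomes: "Secondary outcomes are changes in HRV and interventional acceptability".

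The Data analysis plan models change scores and also enters the baseline value of the outcome as a covariate.

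**The concern.** A baseline used for a change score or as a covariate must not be open to influence by treatment. Here the harness goes on as participants leave the visit at which the method is selected, and practice is scheduled for every evening until the next visit. The first recorded night therefore appears to be treated in one arm and untreated in the other. Any effect of practice on that night's HRV enters the intervention arm's baseline and is then partly or wholly removed from its estimated benefit.

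At stake is the nocturnal part of the HRV outcome, which serves part (b) of the first study aim, restoration of autonomic balance. No later model can recover a pre-treatment night that was never recorded.

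**Working it through.** The article gives no effect size, SD or power for nocturnal HRV, so there is no figure of its own to reproduce. The check has two parts.

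**1. Order of events.** Allocation is disclosed just before visit 1. Resting HRV is recorded, then the three methods are played, then the data are processed to identify the best method, then the harness is fitted. The practice period (4 weeks) equals the interval between visits (4 weeks), so practice fills the interval only if it starts on the evening of visit 1. The log issued at visit 1 covers the following 4 weeks, and in it the intervention arm records practice time daily. No practice-free first evening is described. The baseline night is thus certainly after allocation and, on the plain reading, is the first practice night in the intervention arm only. Hearing the three methods in the laboratory is common to both arms and does not separate them.

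For week 4 the text is open. The description of the second visit does not mention fitting a harness. Controls are offered their method at or on completion of that visit. Data collection also says controls will have practised for 4 weeks by the online assessment 8 weeks after the first visit, which implies a start at about visit 2. Nothing states whether the week-4 recording comes before or after that start.

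**2. Effect on the contrast.** Let T be the cumulative effect of practice on nocturnal HRV, a the same-night effect, b the fitted slope of week-4 on baseline HRV, and p the share of controls who practise on the week-4 night. With baseline as a covariate, modelling the change or the week-4 value gives the same treatment estimate, so the relevant weight is b. It would be 1 only for an unadjusted change score.

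- Intervention arm: baseline a, week 4 T + a.
- Control arm: baseline 0, week 4 p × a.
- Expected contrast: (T + a − p × a) − b × a.

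Take the week-4 difference D = T + a as the target and write f = a / D. The expected contrast as a share of D is then 1 − b × f − p × f. All of f, b and p are assumptions.

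For p = 0 (baseline exposure only):

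- f = 0: 1.00 for any b.
- f = 0.25: 1 − 0.7 × 0.25 = 0.825 (0.875 at b = 0.5; 0.75 at b = 1).
- f = 0.5: 1 − 0.7 × 0.5 = 0.65 (0.75 at b = 0.5; 0.50 at b = 1).

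If half of controls also practise on the week-4 night (p = 0.5, b = 0.7):

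- f = 0.25: 1 − 0.175 − 0.125 = 0.70.
- f = 0.5: 1 − 0.35 − 0.25 = 0.40.

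To give this a scale, borrow 64 per arm, 10% attrition and alpha 0.013 from Sample size estimates (set there for self-report measures). Assume D = 0.6 SD, with the SD of the analysed quantity held at 1. Completers per arm are 64 × 0.9 = 57.6, the standard error is √(2/57.6) = 0.186, and the two-sided critical value is 2.484. Power is Φ(0.6 × share / 0.186 − 2.484):

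| f | p | Share of D (b = 0.7) | Power |
|---|---|---|---|
| 0 | any | 1.00 | 77% |
| 0.25 | 0 | 0.825 | 57% |
| 0.5 | 0 | 0.65 | 35% |
| 0.25 | 0.5 | 0.70 | 41% |
| 0.5 | 0.5 | 0.40 | 12% |

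If the baseline night precedes all practice and the week-4 night precedes the offer to controls, both terms vanish and the share is 1.00.

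**The case against.** The strongest reply has four parts.

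First, the article never names the first practice evening, its schedule and flow figures are not shown here, and it condenses a fuller document. A practice-free first night is possible. But nothing in the text suggests one, and the matching 4-week periods point the other way. In either case the recording is after allocation.

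Second, the same-night effect is not documented. The article describes HRV rising during about 10 minutes of awake listening and does not say that this carries into sleep. This stands: with a = 0 there is no bias, and with a negative effect the direction reverses.

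Third, the direction also depends on the target. If the aim is the cumulative effect T alone, the bias is a × (1 − p − b). With p = 0 that is zero at b = 1 and, for a > 0, away from the null at b < 1. This stands too, so attenuation can be claimed only for the full week-4 difference and a positive same-night effect.

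Fourth, laboratory resting HRV is recorded before any method is played, and autonomic activity is assessed again at visit 2, on completion of which controls are offered theirs. The autonomic aim therefore has one contrast free of this timing problem, and nocturnal HRV is only one component of a secondary outcome. This limits the importance of the point but does not repair the nocturnal measure.

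A reader might go further and infer that the week-4 night in controls is certainly exposed, or that the nocturnal result could come out reversed. The documents do not support either. The second fitting time is not given. With p = 0 the expected contrast is T + a × (1 − b), which cannot be negative when T and a are at least zero and b is at most 1. A reversal under those conditions needs control practice on the week-4 night, which is not established.

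**Conclusion.** The point holds for nocturnal HRV. The baseline night is recorded after allocation and, on the stated schedule, on the intervention arm's first practice evening. It is not a valid pre-treatment value for the change score or the covariate.

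The size cannot be fixed from the article. If practice raises HRV on the same night, the week-4 difference is attenuated by the baseline slope times that effect. Under the assumed values with b = 0.7, 0.825 or 0.65 of the difference remains. If the week-4 harness is fitted at visit 2 and controls start that evening, the contrast shrinks further, but this is conditional because the timing is not stated. Laboratory resting HRV and the self-report primary outcomes are unaffected by this timing. The matter is worth correcting, though it does not threaten the trial's main comparison.

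**What to change.** Reconcile Data collection, Autonomic assessment, Personalised relaxation intervention, and Sleep and symptom monitoring on three things: when each harness is fitted, which evening practice begins, and when controls receive their method. The order should be that the baseline 24-hour recording is complete before the assigned method is handed over, and the week-4 recording is complete before controls receive theirs.

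Recruitment began in April 2017 (Trial status), so some participants may already have been recorded in the present order. For them, do not use night 1 as a baseline. Analyse week-4 nocturnal HRV with the laboratory resting HRV taken before any method was played as the covariate, and record whether controls practised on the week-4 night.

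The cost is that hand-over moves by about a day around each recording. The method is already available online, so hand-over need not require an extra visit. For participants already recorded, a short awake resting measure may predict nocturnal HRV less well than a nocturnal baseline would, so some precision may be lost.
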